#### Secondary Outcome Measurements

##### Satisfaction Scores

Residents in both groups completed a satisfaction questionnaire after each procedure, allowing them to self-assess their satisfaction with the learning outcomes.

The satisfaction survey used a 5-point Likert scale, with 1 indicating strong disagreement and 5 indicating strong agreement. A similar satisfaction survey was administered to the mentors in each group.

##### Patient-Related Outcomes and Complications

Intraoperative unfavorable incidents will be classified according to the Oslo Classification of Intraoperative Unfavorable Incidents [31].

Grade 1: minor incidents with no consequences (eg, minor bleeding controlled immediately and small gallbladder perforation with minimal spillage)Grade 2: incidents requiring intervention but not affecting the procedure’s outcome (eg, moderate bleeding requiring additional hemostatic measures and bile spillage requiring irrigation)Grade 3: incidents significantly affecting the procedure (eg, conversion to open surgery, common bile duct injury, and bowel injury).

This classification complements the Clavien-Dindo Classification, which captures postoperative complications [32]. By applying both systems, a comprehensive assessment of intraoperative and postoperative morbidity will be achieved. Interventions by the attending consultant surgeon and conversions to laparotomy will also be assessed.

### Sample Size

This pilot RCT is designed to identify challenges and unforeseen pitfalls in conducting a proper RCT. Given the novelty of the topic and the resources required for an RCT, it is necessary to conduct a pilot study to assess the feasibility of a full-scale RCT.

The full RCT is designed as a superiority trial to demonstrate the superiority of telementored resident skill acquisition in the OR compared with standard training methods. Previous investigations have shown that the SD of the GOALS score is 2.5. We hypothesize that the intervention group will demonstrate significant clinical improvement in skills, as evidenced by a 3‐ to 5-point increase in the GOALS score relative to the control group. To achieve a statistical power of 0.8, a significance level (*P* value) of <.05, and to account for an expected dropout rate of 20%, 12 residents per group are required for an RCT.

This pilot study will include 5 residents in both the experimental and control arms (n=10). Residents will be stratified into 2 groups according to the number of prior LCs.

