**Methods:**

Eligible residents will be randomly assigned in a 1:1 ratio to either the intervention group (real-time ST and postoperative coaching) or the control group (traditional intraoperative hands-on teaching). This research adheres to the extended SPIRIT (Standard Protocol Items: Recommendations for Interventional Trials) statements for pilot RCTs and follows the intention-to-treat principle. Residents in both groups will perform 5 consecutive procedures under standardized intraoperative conditions. The primary outcomes are the Global Operative Assessment of Laparoscopic Skills (GOALS) score and the Non-Technical Skills for Surgeons (NOTSS). We hypothesize that the intervention group will show a 3- to 5-point improvement in the GOALS score compared with the control group. To achieve 0.8 statistical power, a *P* value <.05, and a 20% dropout rate in a definitive RCT, 12 residents per group are required. We present a pilot RCT with 5 residents per group. Challenges encountered during the trial will be reported, and amendments will be proposed to assess the need for a future definitive RCT.

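### At the 3-point end of the stated range, 12 residents per group with 20% dropout gives about 67–72% power on a two-sided t test, not 80%

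*Protocol article*

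**What the plan says.** The Sample Size section gives the spread, "Previous investigations have shown that the SD of the GOALS score is 2.5", and a hypothesised gain of 3 to 5 points over control. It sets the operating characteristics, "To achieve a statistical power of 0.8" and "a significance level (*P* value) of <.05", and concludes: "to account for an expected dropout rate of 20%, 12 residents per group are required for an RCT". The Abstract (Methods) repeats both the hypothesis, "We hypothesize that the intervention group will show a 3- to 5-point improvement in the GOALS score compared with the control group", and the result, "and a 20% dropout rate in a definitive RCT, 12 residents per group are required". In both places 12 is presented as already covering the dropout.

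Three inputs to the calculation are not given: which difference between 3 and 5 points was used, whether the test is one- or two-sided, and the number per group before dropout. The Statistical Analysis section names the independent-samples t test for the GOALS comparison, with Mann-Whitney as the fallback.

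**The concern.** A size justified by a range of differences should deliver the stated power at the smallest of them. The Anticipated Outcomes section calls the whole 3- to 5-point range clinically meaningful, so 3 points is a difference the definitive trial would be expected to detect. At 3 points with a two-sided t test, the number needed before any dropout is 12, the same as the number said to include dropout.

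This is the only numerical planning figure for the definitive trial, and informing that trial is the pilot's stated purpose. Going from 12 to 15 per group means 30 residents instead of 24, a 25% increase. That matters for feasibility: the Recruitment Status section reports 5 residents on the first platform and 3 on the second, so 8 between spring 2024 and December 2025.

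**Working it through.** **Inputs from the article.** SD 2.5, difference 3 to 5 points, power 0.80, alpha 0.05 and dropout 20% (Sample Size); 1:1 allocation (Abstract, Methods); independent-samples t test (Statistical Analysis).

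**Assumption.** Two-sided testing, the usual convention. One-sided is tried as well.

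**Formulas.** Standardised difference d = difference / SD. Normal approximation: n per group = 2(z_alpha + z_0.80)² / d². For the t test, n is the smallest whole number at which noncentral-t power reaches 0.80, with 2n − 2 degrees of freedom and noncentrality d·√(n/2). Enrolled number = evaluable n / (1 − 0.20), rounded up.

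**Step 1: can the stated 12 be reproduced with dropout included?** Yes, but only with an input the article does not state.
- One-sided at 3 points (d = 1.2), normal approximation: 2(1.645 + 0.842)² / 1.44 = 8.6, so 9 evaluable; 9/0.8 = 11.25, so 12 enrolled.
- Two-sided at 3.5 points (d = 1.4), normal approximation: 2(1.960 + 0.842)² / 1.96 = 8.01, so 9 evaluable; again 12 enrolled.
- By the t test the exact solutions are 9.34 and 9.08. Rounding to whole residents first gives 10 evaluable and 10/0.8 = 12.5, so 13 enrolled, in both cases. Dividing the unrounded solutions by 0.8 gives 11.7 and 11.3, so 12.

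**Step 2: two-sided size at points in the stated range.**

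| Difference | d | t test: evaluable → enrolled | Normal approximation: evaluable → enrolled |
|---|---|---|---|
| 3 | 1.2 | 12 → 15 | 11 → 14 |
| 3.5 | 1.4 | 10 → 13 | 9 → 12 |
| 4 | 1.6 | 8 → 10 | 7 → 9 |
| 5 | 2.0 | 6 → 8 | 4 → 5 |

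At 3 points the exact t-test solution is 11.94, so 12 evaluable give 80.2% power, and 12/0.8 = 15. Neither end of the range gives 12 enrolled.

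**Step 3: power if 12 per group are enrolled and 20% are lost.** 12 × 0.8 = 9.6, so 9 or 10 evaluable per group.

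| Evaluable per group | 3 points, two-sided t | 3.5 points, two-sided t | 4 points, two-sided t | 5 points, two-sided t | 3 points, one-sided t |
|---|---|---|---|---|---|
| 9 | 66.7% | 79.6% | 89.0% | 97.8% | 78.5% |
| 9.6 | 69.9% | 82.4% | 91.1% | 98.5% | 81.0% |
| 10 | 71.8% | 84.1% | 92.2% | 98.8% | 82.5% |

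By the normal approximation, two-sided power at 3 points is 72.1% with 9 per group and 76.5% with 10, still below 80%.

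**Step 4: the difference at which 12 enrolled does give 80%.** Two-sided t test: 3.52 points with 9 evaluable per group, 3.39 with 9.6, and 3.31 with 10.

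**The case against.** The strongest reply is that the article never says 3 points was the design value and never says the test is two-sided. Twelve lies inside the span of 8 to 15 that the range implies on the two-sided t test. It is more than enough at 4 points, the midpoint, where 10 suffice. From about 3.5 points upward the two-sided power is roughly 80% or better.

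That reply stands against one tempting inference. Because 12 equals the evaluable number at 3 points, a reader might conclude that the inflation for dropout was left out. The documents do not support this. Both places say the dropout is included, no pre-dropout number is printed, and two ordinary choices lead to 12 after inflation. The coincidence is suggestive, no more.

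The reply does not rescue the claim of 80% power across the stated range. A design value of 3.5 points appears nowhere. No section mentions a one-sided test. The directional wording, "The full RCT is designed as a superiority trial to demonstrate the superiority of telementored resident skill acquisition", does not by itself fix sidedness, and the Discussion (Principal Findings and Interpretation) allows for telementoring doing worse, which a one-sided superiority test would not assess. Nor is this detail that an article leaves to a fuller document: the figure and its main inputs are printed, so the sum can be checked as it stands.

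A reader might also infer that the present trial is underpowered because of this figure. It is not affected. The pilot enrols 5 per arm irrespective of the calculation, and the Introduction lists refining the definitive sample size among the pilot's aims.

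**Conclusion.** The point holds with a condition attached. With SD 2.5 and a two-sided 5% t test, 12 enrolled residents per group with 20% loss give about 67–72% power at 3 points. To reach 80% there, 15 per group are needed by the t test, or 14 by the normal approximation. The shortfall is confined to the bottom of the range and disappears at somewhere between 3.3 and 3.5 points, depending on whether 10 or 9 per group remain evaluable.

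The conclusion rests on two assumptions: two-sided testing, and dropouts contributing no GOALS data. The second agrees with the available-case analysis in the Data Monitoring section, which is stated for the pilot.

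Severity is moderate. The figure is provisional and belongs to a trial still to be designed, but as printed it does not support the power claimed for the range claimed.

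**What to change.** In the Abstract (Methods) and in Sample Size, state one design difference, the sidedness of the test, and both the evaluable and the enrolled number per group. Then use whichever of these is true:

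- If the target is 3 points two-sided: 12 evaluable and 15 enrolled per group (30 in total) for 80% power with 20% dropout.
- If 12 enrolled per group is to stay: say that, two-sided, 80% power is reached only from about 3.5 points, and that power at 3 points is about 70%. If a one-sided test was intended, state it and give the reason.

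The cost is one reworded sentence in two places. The pilot's size, conduct and analysis do not change. If the first option is taken, the definitive trial's planning target rises by 6 residents.

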### Data Collection and Management

Each video recording will be stored in the OR recording system. The video recordings will be edited by KB (corresponding author) into predefined segments of the surgical procedure, as specified in the stepwise procedure description. The edited video recordings will be annotated. These standardized, edited recordings will be anonymized and randomized for each resident and distributed to the evaluation group for assessment of GOALS and NOTSS scores.

The project secretary will provide each evaluation group with a Questback questionnaire to collect their assessments. The project secretary, who holds the anonymization and randomization key, will then collect and decode the assessments.

Data will be collected and managed using REDCap, hosted at the University Hospital of Northern Norway [33]. Data items (resident satisfaction and mentor satisfaction) will be collected immediately after each procedure. Given the pilot nature of this study, no formal steering committee or data safety monitoring board was established.

GOALS and NOTSS scores will be collected by giving the mentor group 1 month to assess the video records. Patient-related data will be collected retrospectively by reviewing the electronic health record. The timeline of data collection is shown in Figure 5.

**Figure 5. F5:**
[figure not shown]
Trial data collection timeline. GOALS: Global Operative Assessment of Laparoscopic Skills; NOTSS: Non-Technical Skills for Surgeons.

### Statistical Analysis

The primary analysis will compare mean GOALS scores between the intervention and control groups. An independent-samples *t* test will be used for this comparison, provided that the assumption of normality is met; if normality is violated, the nonparametric Mann-Whitney *U* test will be applied. Effect sizes will be calculated using Cohen *d* to quantify the magnitude of the difference between groups and to inform sample size estimation for a future definitive RCT.

Secondary analyses will include comparisons of NOTSS scores between the intervention and control groups using the same statistical approach as that used for the primary outcome. Within-group improvement in technical performance across the training period will be assessed by comparing GOALS scores from the first to the fifth procedure using paired *t* tests. Participant satisfaction scores will be compared between groups using the Mann-Whitney *U* test, as these data are collected on an ordinal Likert scale.

Multivariate analyses will be conducted using linear regression models to examine the association between group allocation and GOALS scores while adjusting for potential confounding factors. Group allocation (intervention vs control) will be included as the primary predictor. Covariates will be selected a priori based on theoretical relevance and will include baseline surgical experience (defined as completion of 5‐10 vs 10‐20 prior LCs), baseline GOALS score from the first procedure, year of residency training, study site (Sandnessjøen vs Mo i Rana), and indicators of procedure complexity, including intraoperative findings and operative time.

Exploratory analyses will be performed to further characterize performance development and relationships between outcomes. Learning curves across the 5 procedures will be evaluated by examining trajectories of GOALS scores using repeated-measures ANOVA or mixed effects models, depending on the data structure and model assumptions. Subgroup analyses stratified by baseline experience level will be undertaken, and correlations between GOALS and NOTSS scores will be assessed to explore the relationship between technical and nontechnical performance.

As this study is a pilot trial, feasibility outcomes will be summarized descriptively. These outcomes will include the recruitment rate, expressed as the number of participants enrolled per month; balance between randomized groups; adherence to the study protocol (including completion of all 5 procedures and scheduled coaching sessions); the frequency and nature of technical failures related to the telementoring system; and withdrawal rates, along with reasons for withdrawal. Participants may withdraw from the study at any time. In cases where a resident discontinues the intervention, outcome data will be collected, where feasible, and analyzed using the intention-to-treat principle.

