### Allocation and Blinding

The randomization process will use a predetermined statistical sequence generated by an external researcher who was not directly engaged in the study. The allocation sequence will be concealed using a centralized web-based randomization system. Personnel enrolling participants will not have access to the sequence until after enrollment. All individuals who actively participate in the experiment will be granted access to the allocation codes after randomization. Residents are enrolled by KB. After enrollment confirmation, the allocation is revealed by KB.

Computer-generated stratification will be used for randomization to create balanced and unpredictable groups. To ensure balance across groups with respect to significant confounders, the randomization process will be stratified by trainees’ experience, explicitly distinguishing between those who had performed 5 to 10 LCs and those who had performed 10 to 20.

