### Outcomes

#### Primary Outcomes

The primary outcomes are the GOALS and NOTSS scores (Figures 1 and 2). The GOALS score is the only global rating scale developed and validated for assessing laparoscopic surgery. Five subscales are assessed: depth perception, bimanual dexterity, efficiency, tissue handling, and autonomy. Each subscale is scored from 1 to 5, yielding a maximum score of 25 when assessing the resident’s laparoscopic technical skills. The NOTSS score assesses the operating surgeon’s nontechnical surgical skills by evaluating defined parameters [30].

The NOTSS score will be derived from video recordings of interactions between the operating telementee and the rest of the OR team. A 3-member evaluation group of specialized OR nurses will be established to assess the NOTSS score for each procedure by reviewing video footage from the room camera.

The GOALS score will be assessed by video recording the laparoscopic camera footage of each procedure performed by the included registrars. A 3-member evaluation group of expert laparoscopic surgeons will be established to assess the GOALS score for each procedure by reviewing the laparoscopic video footage, including the verbal communication between the mentee and the mentor.

Both evaluation groups will be presented with video footage of each included mentee in a random order to obtain blinded evaluations of the GOALS and NOTSS scores.

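### The between-group analyses do not fix the resident as the unit of analysis, and the linear regression as listed works only on procedure rows, where it ignores clustering within resident

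*Protocol article*

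**What the plan says.** Residents are the randomised unit, 1:1, with five per arm in the pilot (Study Design and Setting; Sample Size). Each is measured repeatedly:

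- Abstract, Methods: "Residents in both groups will perform 5 consecutive procedures under standardized intraoperative conditions".
- Primary Outcomes: "A 3-member evaluation group of expert laparoscopic surgeons will be established to assess the GOALS score for each procedure". NOTSS is likewise scored for each procedure, by three nurses.
- Satisfaction Scores: "Residents in both groups completed a satisfaction questionnaire after each procedure".

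The Statistical Analysis section states "The primary analysis will compare mean GOALS scores between the intervention and control groups". The method is a two-sample t test if the scores look normal, with Mann-Whitney U as the fallback. NOTSS follows the same approach, and satisfaction is compared by Mann-Whitney U. Cohen d from the comparison is meant to help size the definitive trial.

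The section then adds: "Multivariate analyses will be conducted using linear regression models to examine the association between group allocation and GOALS scores". Besides arm, the covariates are prior experience in two categories, first-procedure GOALS, residency year, site, intraoperative findings and operative time.

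Repeated-measures ANOVA or mixed models are named only for the exploratory learning curves. Allocation and Blinding states "Computer-generated stratification will be used for randomization to create balanced and unpredictable groups" and gives the strata as 5 to 10 versus 10 to 20 prior cholecystectomies.

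**The concern.** Five scores from one resident are likely to be correlated. The t test, Mann-Whitney U and ordinary linear regression all assume independent observations, and the section nowhere says that the five scores are reduced to one per resident or that the between-group models carry a resident term. If procedures are the rows, standard errors are too small, intervals too narrow and P values too low.

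This matters even in a pilot. The Data Presentation section puts the emphasis on effect sizes and confidence intervals, and those are what the wrong unit distorts. Cohen d also feeds the sample size of the next trial, so the SD in its denominator has to be defined. With the unit left open, it could be chosen after the data are seen.

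**Working it through.** **Inputs from the protocol.** Five residents per arm; five procedures per resident; SD of GOALS 2.5; difference 3 to 5 points; power 0.8; significance level .05 (taken as two-sided); dropout 20%; 12 residents per group stated for the definitive trial. **Assumed.** Within-resident ICC 0.1 to 0.7, because the protocol gives none. The three raters' scores are taken as already combined into one score per procedure.

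**1. The plan's own figure.** n per group = 2(1.96 + 0.8416)² × SD² / difference².
- Difference 3: 2 × 7.85 × 6.25 / 9 = 10.9, so 11; 11/0.8 = 13.75, so 14.
- Difference 3.5: 2 × 7.85 × 6.25 / 12.25 = 8.01, so 9; 9/0.8 = 11.25, so 12.

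The stated 12 is therefore met at a difference of about 3.5, or at 3 with a one-sided test (9, then 12). It does not depend on the present point. It does show that the plan counts residents when sizing the trial, and that the SD of 2.5 is not tied to a single procedure or to a five-procedure mean.

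**2. Can the regression run on residents?** Arm, experience, first-procedure GOALS, residency year, site, intraoperative findings and operative time make at least 7 predictors. With the intercept that is 8 parameters, so ten resident rows leave at most 10 − 8 = 2 residual df. Two of the covariates differ between a resident's procedures. First-procedure GOALS as a covariate points to later procedures as outcomes. The model is workable only on procedure rows: 10 × 4 = 40 if the first procedure is the baseline.

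**3. Cost of procedure rows.** Design effect = 1 + (5 − 1) × ICC; its square root is the ratio of true to naive standard error for 25 versus 25 scores. Type I error at nominal 5% was simulated under no arm effect (20,000 runs for the tests; 2,000 for the regression on procedures 2 to 5 with the listed covariates, stratum included).

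| ICC | Design effect | SE ratio | t test, 25 v 25 | Mann-Whitney, 25 v 25 | Regression, 40 rows |
|---|---|---|---|---|---|
| 0.1 | 1.4 | 1.18 | 9.7% | 8.9% | 7.9% |
| 0.3 | 2.2 | 1.48 | 19.7% | 18.2% | 14.1% |
| 0.5 | 3.0 | 1.73 | 28.0% | 26.1% | 20.5% |
| 0.7 | 3.8 | 1.95 | 34.7% | 32.1% | 23.8% |

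A t test on one mean per resident (5 v 5, 8 df) gave 4.8% to 5.2% throughout.

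**4. The stratum.** The regression includes it; the t test and Mann-Whitney U do not. With resident means and strata balanced across arms, the unadjusted t test has a type I error of 3.0% if the strata differ by 1 SD and 0.6% if they differ by 2 SD. That is conservative, the opposite direction to clustering. Adjusting costs 1 df: the critical t goes from 2.306 (8 df) to 2.365 (7 df). It narrows the interval only if the stratum explains more than 1 − (2.306/2.365)² ≈ 5% of the variance of resident means. At an assumed 25%, 2.365 × √0.75 = 2.05 against 2.306, about 11% narrower.

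**5. Cohen d.** SD of a five-procedure mean divided by SD of one procedure = √(ICC + (1 − ICC)/5): √0.44 = 0.66 at ICC 0.3 and √0.60 = 0.77 at ICC 0.5. Since n varies with SD², the implied sample size differs by 1/0.44 ≈ 2.3-fold or 1/0.60 ≈ 1.7-fold according to which SD is used.

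**The case against.** The strongest reply is that the protocol nowhere enters 25 rows per arm into the t test. A comparison of mean GOALS scores can mean one mean per resident. Both trials are sized in residents, and the first-to-fifth paired t test naturally uses one pair per resident. On that reading the t test is valid. The article is also condensed, and an analysis plan that is not shown may settle the unit.

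This stands for the t test and Mann-Whitney U. A reader might infer that the standard errors and P values of every named analysis are wrong; the document does not support that, because for these two tests the fault is conditional. It does not rescue the regression, whose covariates the article itself fixes and which is barely estimable on ten rows.

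A reader might also infer that all the analyses ignore the randomisation stratum. That is not so: the regression lists experience in the same two categories, and the omission from the unadjusted tests errs on the safe side.

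The ICC is an assumption. At 0.05 the pooled t test gives only 7.5%. Nor is a single-procedure SD in Cohen d wrong in itself; the right one depends on the definitive trial's endpoint. Lastly, the protocol disclaims definitive conclusions on effectiveness, which limits the harm from a false positive but not from intervals that are too narrow.

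**Conclusion.** The concern holds in limited form. The unit of analysis for GOALS, NOTSS and satisfaction is not fixed, although each resident contributes five scores. The linear regression, as listed, is either left with at most 2 residual df on resident rows or run on procedure rows with understated standard errors: type I error about 8% to 24% over an assumed ICC of 0.1 to 0.7.

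For the t test and Mann-Whitney U the inflation (about 10% to 35% and 9% to 32% over the same range) arises only if procedures are the rows. With one mean per resident, the t test holds its level. Leaving the stratum out of the unadjusted tests does not threaten validity, but it can cost precision.

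All percentages rest on the assumed ICC, normal scores, complete sets of five procedures and, for the regression, covariates unrelated to the outcome apart from first-procedure GOALS.

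**What to change.** State that the resident is the unit of analysis.

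- **Primary GOALS analysis.** Use a linear model on each resident's mean over procedures 1 to 5 with arm and experience stratum (7 df). Alternatively, use a mixed model with arm, stratum, procedure number and a random resident intercept, with small-sample df. The two give the same arm effect only when all five procedures are present. With incomplete sets the mixed model allows for which procedures are missing.
- **NOTSS and satisfaction.** Apply the same rule to NOTSS, and compare satisfaction on one summary per resident.
- **Covariate-adjusted model.** Any model with procedure-level covariates needs a resident random effect and fewer terms than now listed.
- **Cohen d.** Say whether the SD is that of a resident mean or of a single procedure, and report the between-resident SD and the ICC for sizing the definitive trial.
- **Optional.** Drop the normality check as the switch between tests.

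The change is to wording. No new data are needed, and mixed models are already among the planned exploratory methods. It does require an amendment, which the Ethical Considerations section says goes to the ethics committee, and it should be dated before the analysis planned for November 2026. The statistical price is wider intervals than a 50-row analysis would show, and one df spent on the stratum.

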## Methods

### Study Design and Setting

This study is a parallel, 2-group, assessor-blind, multicenter pilot RCT. Participating surgical residents are allocated in a 1:1 ratio to either the intervention group, which receives real-time intraoperative telementoring and postoperative coaching, or the control group, which receives traditional intraoperative mentoring. The intention-to-treat principle will be applied. The study adheres to the latest SPIRIT (Standard Protocol Items: Recommendations for Interventional Trials) 2025 statements recommended for RCT protocols, as shown in Checklist 1 [26].

The Northern Norwegian Health Care Trust comprises 11 hospitals, including 1 university hospital and 10 local hospitals. Four hospitals within the Northern Norwegian Health Care Trust were initially assessed for eligibility as study sites: Sandnessjøen, Mo i Rana, Stokmarknes, and Bodø. Following a feasibility assessment, 2 hospitals—Sandnessjøen and Mo i Rana—were selected as active study sites based on surgical volume, resident availability, geographic location for ease of patient and resident inclusion in the study, and telementoring infrastructure, including the availability of telementors and on-site mentors. Stokmarknes and Bodø were not included as active recruitment sites due to anticipated pressure from acute cases in these locations, which would affect the elective surgical plan that the telementoring project was part of. Additionally, one of the initially included telementors based in Stokmarknes had to withdraw from the study. Although the telementoring infrastructure was initially installed at these locations to support patient and resident inclusion in the study, we ultimately decided to restrict inclusion facilities to Mo i Rana and Sandnessjøen. This facilitated optimal collaboration among actively participating telementors, residents, and the project administrator, KB, who was located in Bodø. Depending on the results of this pilot study, the expansion to include Stokmarknes and Bodø in a definitive RCT will be considered.

For this pilot RCT, 2 of the local hospitals, Sandnessjøen and Mo i Rana, served as study sites. Both locations offer surgical residency training programs that provide LC training.

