### Data Presentation

Continuous variables will be presented as mean (SD) for normally distributed data and as median (IQR) for skewed distributions. Categorical variables will be presented as frequencies and percentages. A *P* value <.05 will be considered statistically significant. Given the pilot nature, emphasis will be placed on effect sizes and CIs rather than *P* values alone. Descriptive statistics and data analysis will be performed using Microsoft Excel - Office 365 and IBM SPSS Statistics software (version 31.0; IBM Corp).

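### A normality check on 5 residents per arm decides whether the primary GOALS comparison is a t test or a rank test; fix one mean-difference analysis instead (minor)

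*Protocol article*

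**What the plan says.** All references are to the protocol article.

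- **Contrast.** Statistical Analysis: "The primary analysis will compare mean GOALS scores between the intervention and control groups".
- **Test.** The next sentence makes the test conditional. The independent-samples t test is used "provided that the assumption of normality is met; if normality is violated, the nonparametric Mann-Whitney" U test is applied. The section names no normality test or threshold, and does not say whether the values are resident means or single procedures.
- **Effect size.** The same paragraph calculates Cohen d whichever test is used, to help size a definitive trial. NOTSS is to be analysed in the same way as GOALS.
- **Weight given to P values.** Data Presentation: "emphasis will be placed on effect sizes and CIs rather than" P values alone. That section also reports means for normally distributed variables and medians for skewed ones.
- **Size.** Sample Size: "This pilot study will include 5 residents in both the experimental and control arms (n=10"). Study Design and Setting: "Participating surgical residents are allocated in a 1:1 ratio".
- **Planning values.** Sample Size: "Previous investigations have shown that the SD of the GOALS score is 2.5". Abstract, Methods: "We hypothesize that the intervention group will show a 3- to 5-point improvement in the GOALS score compared with the control group".

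**The concern.** The data choose the primary test through a preliminary check, and five values per arm are too few for that check to be informative. It will miss most real skewness and will sometimes flag data that are normal.

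The two branches also answer different questions. The t test addresses the mean difference, which is the stated contrast and the quantity behind the 3- to 5-point hypothesis and Cohen d. Mann-Whitney compares ranks and yields neither a mean difference nor Cohen d. If the switch fires, the article could report a P value from one comparison beside an effect size and CI from another, and chance would largely decide whether that happens.

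**Working it through.** **The plan's own figure.** The only sample-size result is 12 per group for the definitive trial (power 0.8, P<.05, 20% dropout). With SD 2.5, a 3-point difference and a two-sided 5% level, the normal approximation gives n = 2 × (1.960 + 0.842)² × 2.5² / 3² = 10.9, so 11, and 11/0.8 = 13.75, so 14. A t-based calculation gives 12 before dropout. A one-sided test gives 9, and 9/0.8 = 11.25, so 12. The stated 12 is thus near what the planning values imply. The article gives no power for the pilot and no property of the normality check, so those are computed here.

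**Inputs.** From the article: 5 per arm, SD 2.5, differences of 3 to 5 points, level 0.05. Assumed: a two-sided test, one value per resident, Shapiro-Wilk at 0.05 in each arm with a switch if either arm is flagged, and the distribution shapes below. Each setting used 20,000 simulated trials (12,000 for the small-effect and outlier settings).

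**Step 1: how well the check discriminates.**

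| True shape | One given arm flagged | At least one arm flagged |
|---|---|---|
| Normal | 5% | 9-10% |
| Uniform | 5-6% | 11-12% |
| t, 3 df | 9-10% | 18% |
| Exponential | 16-17% | 30% |
| Lognormal | 23-24% | 41-42% |

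If each resident's value is the mean of five independent procedures, averaging hides the shape further, and per-arm flagging is 5-12% across the shapes tried.

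**Step 2: the fallback test at 5 v 5.** There are C(10,5) = 252 equally likely rank arrangements. U ≤ 2 covers 4 of them, so the two-sided level is 8/252 = 0.0317. U ≤ 3 covers 7, giving 14/252 = 0.0556, which exceeds 0.05. The exact test can therefore use at most 0.032.

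**Step 3: power under normality, SD 2.5.**

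| Difference | t test always | Mann-Whitney always | Rule as written |
|---|---|---|---|
| 3 | 38.9% | 28.8% | 38.0% |
| 4 | 60.5% | 48.0% | 59.3% |
| 5 | 79.2% | 67.6% | 78.1% |

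The noncentral t gives 38.6%, 60.3% and 79.1% for the first column.

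The cost of the rule is the flag rate times the power lost in flagged trials. At 3 points: 0.095 × (0.364 − 0.272) = 0.009. At 5 points: 0.095 × (0.787 − 0.671) = 0.011. Both agree with the table.

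**Step 4: other shapes (rule minus fixed t test).**

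- Exponential: 47.3 − 48.9 = −1.6 points at a 3-point difference; 75.9 − 80.5 = −4.6 at 5.
- Lognormal: 64.2 − 66.3 = −2.1 at 3; 82.3 − 86.6 = −4.3 at 5. At smaller differences it gains: +2.1 at 1 point and +0.8 at 2 points.
- t with 3 df: 0 to −1 at 3 to 5 points; about +0.3 to +0.5 at 1 to 2 points.
- 10% outliers: +1.1, +1.9 and +1.7 at 1, 2 and 3 points.

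**Step 5: type I error.** Under no difference the rule rejects in 3.5% to 5.0% of trials across the shapes in Step 1.

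**The case against.** The strongest reply is that little depends on the switch. This is a 10-resident pilot, its Limitations section rules out definitive conclusions on effectiveness, and no decision is tied to P<.05. Cohen d is calculated whichever test is used, so the effect size for planning does not change. The normality method and the unit of analysis are details that an article may leave to an analysis plan. All of that stands, and it keeps the priority low. It does not remove the point, because the article itself states the rule for the primary test.

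The percentages also depend on the assumed check. Testing pooled residuals would flag about 4% of normal trials instead of 9-10%. Testing 25 procedures per arm would detect 92% of exponential and 97% of lognormal data, but it would ignore clustering within residents.

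A reader might infer more than the documents support:

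- *That the check cannot detect non-normality and can only cost power.* It flags up to 42% of strongly skewed trials, and the rule gains up to about 2 points with outliers or with strong skew and small effects.
- *That 10 to 12 points of power are lost.* That gap separates always using Mann-Whitney from always using the t test under normality, and the article plans neither.
- *That false positives increase.* They do not (Step 5).

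**Conclusion.** The point holds as a minor one. A check that separates normal from strongly skewed data poorly (about 9-10% of trials flagged against 30-42%) decides whether the primary P value addresses the stated mean difference or a rank comparison. The main harm is that the P value may not match the mean-based effect size and CI reported with it.

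The loss of power is secondary: about 1 point under normality and about 2 to 5 points under exponential or lognormal skew, for true differences of 3 to 5 points. In some other settings the rule gains slightly.

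These sizes assume Shapiro-Wilk at 0.05 per arm, one value per resident, SD 2.5 and a two-sided 5% level. The mismatch between test and stated contrast does not depend on those choices, only on the switch being made.

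**What to change.** Delete the normality condition. State one primary analysis of resident-level mean GOALS: an independent-samples (pooled) t test, or its regression equivalent, with the mean difference and 95% CI. Give Mann-Whitney, or an exact permutation test of the mean difference, as a sensitivity analysis that is always reported. Apply the same to NOTSS.

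Welch's version should not be chosen in the hope of gaining power. With normal data and equal SDs at 5 v 5, its simulated power was 35.9% at 3 points and 77.1% at 5, against 37.4% and 78.5% for the rule as written in the same run. The pooled test gains about 1 point over the rule.

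The change costs one sentence and no new data. Analysis is scheduled for November 2026, so it can be recorded before then.
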